#### Validation phase

In the validation phase the intervention therapy stays the same, but new patients will be included. In this study design, the interest is that treatment success will be higher in the matched group than the unmatched group, which means a one-tailed hypothesis is used to calculate the power. In the validation phase we need 105 patients to detect a minimum clinically important difference (effect size 0.43) with 80% power using a one-tailed hypothesis. This means that three groups of 35 patients are needed to complete the whole trial. Again we assume a dropout rate of 54% into account and therefore aim to include 229 patients.

### Data analysis

#### Derivation phase

This phase aims to detect potential predictive variables for treatment success (dichotomous, yes or no) in a set of baseline measurements. A minimal decrease in the MODI score of six points is considered as treatment success [35].

Potential predictive variables are selected as follows: first, individual variables from the self-reports, history and physical examination are tested for their bivariate association with the reference standard using independent sample t tests, Mann-Whitney U tests or chi-square tests based on the nature of the data. Variables with a significance level of *P* <0.10 are retained as potential prediction variables. We chose a more liberal significance level at this stage to avoid excluding potential predictive variables.

Next, selected potential prediction variables and known predictors as determined in the study of Hicks *et al*. [16] are entered into a multiple linear regression equation to determine the optimal set of predictors. A significance of *P <*0.05 is used in this stage. Variables retained in the regression model are used to develop a multiple CPR for classifying patients as likely responders to treatment. This statistical analysis is performed for each treatment group (motor control therapy, general active exercise therapy and isometric training therapy).

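### Derivation phase: a yes/no success target is followed by a linear regression with no named dependent variable and, separately, P-value selection from 28 items within small arms is prone to pick noise

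*Protocol article*

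**What the plan says.** Protocol article, Data analysis, Derivation phase:

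- **Target.** The aim is to "detect potential predictive variables for treatment success (dichotomous, yes or no) in a set of baseline measurements". Success is then defined: "A minimal decrease in the MODI score of six points is considered as treatment success".
- **Screening.** Candidates come from questionnaires, history-taking and clinical tests. Each is to be "tested for their bivariate association with the reference standard using independent sample t tests, Mann-Whitney U tests or chi-square tests", with the test chosen by type of data. "Variables with a significance level of *P* <0.10 are retained as potential prediction variables". The reason given is: "We chose a more liberal significance level at this stage to avoid excluding potential predictive variables".
- **Model.** The "selected potential prediction variables and known predictors as determined in the study of" the earlier single-arm motor control study "are entered into a multiple linear regression equation to determine the optimal set of predictors". Retention is at P<0.05, and the whole analysis is run separately for each of the three treatment groups. The retained variables form a rule that classifies patients as likely responders.

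Elsewhere in the article:

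- Measurements and Table 3 class MODI as the primary (dependent) measure and every other item as secondary (independent).
- The Power analysis sizes this phase at three groups of 40, raised to 260 for 54% dropout. The basis is a group-difference effect size of 0.43, not the number of candidate predictors or outcome events.
- The rules are then tested in a new randomised sample, with a recruitment target of 229.

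**The concern.** There are two separate problems.

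**Model and outcome do not match.** The target and the screening tests are binary, but the named model is the one normally used for a continuous outcome. If its dependent variable is success, logistic regression is the natural model. If it is MODI change or the nine-week score, linear regression is admissible, but it then fits a different quantity from the stated target and from the one used in screening. The text does not let an analyst decide.

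**Selection in small arms.** Two rounds of P-value selection from many candidates, repeated in three small arms, tend to give a rule that looks accurate in the data that produced it, whether or not anything predicts response.

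A connected point is baseline MODI. It is listed only as the outcome, yet a six-point fall depends on the starting score. The entry criteria set no minimum, so a patient who starts below six points cannot succeed.

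Deriving the rules is the trial's first objective. The matched/unmatched split, the validation pre-stratification and the second sample all rest on them.

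**Working it through.** **Inputs**

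- Candidates: Table 3 rows other than MODI are 14 impairments + 3 activity and participation items + 11 contextual factors = 28. There are more if questionnaire subscales are tested separately.
- Thresholds: P<0.10 at screening, P<0.05 in the model (Derivation phase).
- Patients per arm, from the Power analysis: 120/(1 − 0.54) = 261, which reproduces the stated 260. Recruited per arm: 260/3 = 86.7, about 87. Completers per arm: 260 × 0.46/3 = 39.9, about 40. Intention-to-treat is specified, so the analysed n lies between about 40 and 87.
- Assumed, because the article gives no figure: success rate (33–70% for events, 50% in the simulations), and independent, normally distributed predictors.

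**Step 1: false positives at screening, no true predictors**

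- Expected number: 28 × 0.10 = 2.8 per arm, or 8.4 over three arms.
- Chance of at least one in an arm, if independent: 1 − 0.90^28 = 0.95.

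Neither figure depends on n.

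**Step 2: outcome events per candidate**

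Formula: n × min(success rate, 1 − success rate)/28.

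| Success rate | n = 40 | n = 87 |
|---|---|---|
| 33% | 13.2/28 = 0.47 | 28.7/28 = 1.03 |
| 50% | 20/28 = 0.71 | 43.5/28 = 1.55 |
| 70% | 12/28 = 0.43 | 26.1/28 = 0.93 |

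**Step 3: the two selection steps on pure noise**

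Each simulated arm has 28 unrelated normal variables, a t-test screen at P<0.10, then backward linear regression at P<0.05. Apparent AUC is averaged over arms that yield a rule.

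| | n = 40 | n = 87 |
|---|---|---|
| Variables passing the screen | 2.8 | 2.8 |
| Arms yielding a rule | 78% | 79% |
| Apparent AUC | 0.77 | 0.69 |
| AUC in new patients | 0.50 | 0.50 |

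Entering four extra variables regardless of the screen, to stand for the earlier study's predictors, gives about 80% and 0.78 at n=40. More patients lower the apparent AUC but not the share of arms with a false rule.

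**Step 4: with true predictors**

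Four true predictors, by log odds ratio per SD. In the rows marked with an asterisk, those four enter the model regardless of the screen.

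| n | Log-OR | False share of retained variables | Apparent AUC | AUC in new patients |
|---|---|---|---|---|
| 40 | 0.3 | 72% | 0.79 | 0.53 |
| 40 | 0.5 | 54% | 0.82 | 0.58 |
| 40 | 0.7* | 39% | 0.85 | 0.65 |
| 87 | 0.3 | 55% | 0.72 | 0.55 |
| 87 | 0.5 | 35% | 0.77 | 0.63 |
| 87 | 0.7* | 24% | 0.83 | 0.73 |

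**Step 5: does the linear model cause this?**

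At n=40 with four true predictors (log-OR 0.5) and four further variables entered regardless of the screen, linear and logistic backward elimination give false shares of 58% and 57%, and new-patient AUC of 0.576 and 0.575. With three noise predictors and 50% success, the linear model's type I error is 4.9%. With one true predictor (log-OR 0.7), the two models agree on P<0.05 in 98.6% of tests. The answer is no.

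**The case against.** **The dependent variable may be continuous.** Measurements calls MODI the dependent measure, and the validation analysis names the MODI score as its dependent variable. A linear model could be intended. This stands, so it cannot be said outright that the model is wrong. The conflict with the binary target and the binary screening remains.

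**A reader might infer that linear regression invalidates the P<0.05 retention, or gives unusable probabilities outside 0 to 1.** The article does not support this. Step 5 shows almost the same retention under either model. The rule is built from the retained variables, and no predicted probability is planned.

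**A reader might infer that the rules will mostly fit noise.** That depends on assumed effects and on n. It holds for absent or weak predictors at n=40. It fails at n=87 with moderate to strong predictors (false share 24–35% in step 4). Real candidates are also correlated (height, weight and BMI, for instance), and some are categorical.

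**Baseline MODI may already be covered.** It is a self-report taken at baseline, and self-reports are screened. The article neither includes nor excludes it clearly, and gives no figure for how many patients would enter below six points. The request is therefore to state it.

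**Validation in new patients is planned, and shrinkage or bootstrap details may sit in an analysis plan that is not shown.** Both are fair. Their absence alone is not the point. What the article does fix is the two-stage P-value selection within each arm. Validation can expose a false rule, but only after up to 229 more patients are enrolled, and it does not repair the derivation.

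**Conclusion.** The point holds in two parts.

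1. The Derivation phase text is internally inconsistent: a binary target and binary screening, followed by a linear regression whose dependent variable is not stated. This needs no assumption beyond the plain reading. In numerical effect, linear versus logistic is minor.
2. The selection procedure is prone to pick noise. About 2.8 false positives per arm are expected at screening. With nothing to find, about 78–80% of arms still produce a rule, with apparent AUC about 0.77 at n=40 and 0.69 at n=87 against a true 0.50. These figures assume independent normal predictors and, for the simulated ones, 50% success. With true predictors the optimism shrinks but persists across the range examined.

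The cause of the second part is many candidates, P-value selection and small arms, not the linear model. The material does not show that the rules must be mostly noise. Since the whole validation phase rests on these rules and the change is confined to the analysis, it should be made before the derivation data are analysed.

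**What to change.** - Name the dependent variable. Use logistic regression for success, or model continuous nine-week MODI and apply the six-point cut to the prediction.
- Include baseline MODI explicitly as a predictor.
- Replace univariable P<0.10 screening by a penalised fit on a short candidate list fixed in advance, which includes the previously published predictors.
- Bootstrap the whole selection process, and report optimism-corrected discrimination and calibration before the rules are carried into validation. A bare requirement that corrected AUC exceed 0.5 should not serve as the gate, because it has no margin: in a check of the screen-and-backward procedure on noise alone, 89% of rules passed it at n=40 and 75% at n=87.

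Changing linear to logistic alone would settle the wording but not the overfitting.

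Cost: revised analysis text and modest extra programming, with no change to recruitment or measurements. Reported accuracy will be lower.

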#### Validation phase

In the validation phase new patients will be again assigned randomly into one of the three treatment groups. Based on the derived CPR determined in phase one, each intervention group will be divided into either ‘matched therapy’ or ‘unmatched therapy’. The recruitment, information form, informed consent, measurements, blinding and intervention procedure will be the same for both derivation and validation phase.

To verify intergroup differences at baseline, variables will be compared between groups using independent t tests, Mann-Whitney U tests, or chi-square tests of independence based on the nature of the data.

To examine the principle hypothesis (difference in treatment effect between matched and unmatched groups), a three-way repeated-measures analysis of variance will be performed with treatment group (motor control versus general active exercise therapy vs. isometric therapy) and classification subgroup (motor control versus general active exercise therapy versus isometric therapy) as between-subject variables and time (baseline, nine weeks, six months and one year) as the within-subject variable. The dependent variable is disability (MODI score). The hypothesis of interest is the three-way interaction, and the two-way interactions between time and treatment group and between time and classification subgroup. We hypothesize that outcome over time will not differ based on the randomized treatment group, or the classification subgroup, but will depend on the interaction between the treatment group and classification subgroup, such that patients randomized to matched treatment will have better outcomes than patients randomized to unmatched treatment. This hypothesis will be supported if the three-way interaction is significant, but the two-way interactions are not. Pairwise *post-hoc* comparisons will be performed at each follow-up period to further explore any significant interaction terms. In both the derivation and validation phase we will use an intention-to-treat analysis.

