**Methods/Design:**

The study design is a randomized controlled trial. Patients with nonspecific CLBP of more than three months duration are recruited at the Antwerp University Hospital (Belgium) and Apra Rehabilitation Hospital. After examination, patients are randomly assigned to one of three intervention groups: motor control therapy, general active exercise therapy and isometric training therapy. All patients will undergo 18 treatment sessions during nine weeks. Measurements will be taken at baseline, nine weeks, six months and at one year. The primary outcome used is the Modified Oswestry Disability Questionnaire score. For each type of exercise therapy a CPR will be derived and validated. For validation, the CPR will be applied to divide each treatment group into two subgroups (matched and unmatched therapy) using the baseline measurements. We predict a better therapeutic effect for matched therapy.

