### Randomization and blinding

In both phases patients will be randomly assigned to one of the three treatment groups after baseline testing. The responsible researcher will use a randomization list generated with Microsoft Excel® software (version 14.3.9, Microsoft Corporation, Zaventem, Belgium). Physiotherapists responsible for the treatment sessions are blinded for the results of baseline and follow-up measurements, which are being performed by the responsible researcher.In the validation phase a pre stratification will be used to ensure a 50:50 ratio between matched and unmatched therapy within one intervention group. Patients who have a strong preference for one of our intervention groups and therefore cannot be randomized will be asked to participate in a parallel cohort study. In this study similar baseline and follow-up measurements will be used.

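### The validation model treats baseline MODI as a fourth outcome time point rather than a covariate, which costs power on the matching hypothesis but does not bias it

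*Protocol article*

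**What the plan says.** The protocol article fixes the principal validation analysis in its Data analysis section, under Validation phase. It is a three-way repeated-measures ANOVA with treatment group and classification subgroup (three levels each) as between-patient factors and "time (baseline, nine weeks, six months and one year) as the within-subject variable". The outcome is stated as "The dependent variable is disability (MODI score", so the baseline score is part of the outcome vector.

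The decision rule is also fixed: "This hypothesis will be supported if the three-way interaction is significant, but the two-way interactions are not". Follow-up comparisons are described only as "Pairwise *post-hoc* comparisons will be performed at each follow-up period to further explore any significant interaction terms".

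No baseline covariate is named. Otherwise, baseline values appear in between-group tests: "To verify intergroup differences at baseline, variables will be compared between groups using independent t tests". No consequence for the model is attached to those tests.

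The covariate is available. The abstract says "Measurements will be taken at baseline, nine weeks, six months and at one year", Table 3 lists MODI at all four times, and Randomization and blinding says "In both phases patients will be randomly assigned to one of the three treatment groups after baseline testing". The Power analysis section says "In the validation phase we need 105 patients to detect a minimum clinically important difference (effect size 0.43) with 80% power using a one-tailed hypothesis".

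**The concern.** Therapy is allocated after baseline MODI is recorded. Within a classification subgroup, therapy therefore cannot have affected the baseline score. Entering that score as a freely estimated outcome level ignores this. The interaction with time uses only within-patient contrasts: follow-up against baseline, and differences among the follow-up visits. Where baseline contributes, it does so by subtraction, which fixes its slope at 1 and carries its full noise into the contrast. Using baseline as a covariate estimates the slope instead.

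What is at stake is the power of the trial's principal hypothesis. With 54% dropout assumed, 229 patients are to be recruited to obtain 105 completers. A prediction rule that works could be declared not validated partly because information already collected was used inefficiently.

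**Working it through.** **The plan's own figures.** The dropout step reproduces: 105/(1 − 0.54) = 228.3, rounded up to 229. The 105 does not reproduce as a one-tailed comparison of two equal groups at 0.43 SD with alpha 0.05: 2 × (1.645 + 0.842)²/0.43² = 66.9, so 67 per group and 134 in total. With 105 patients that comparison has about 71% power. The point here does not depend on how 105 was obtained, but the size gives no visible spare power.

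**Inputs.**
- From the document: 105 completers, effect 0.43, and a 50:50 matched-to-unmatched split within each arm.
- Assumed: alpha 0.05, MODI SD of 1 at every visit, the same correlation ρ between any two visits (reference 0.5, range 0.3 to 0.9), equal class sizes and a common baseline slope.
- The split and equal class sizes give 105/6 = 17.5 patients per matched cell and 105/12 = 8.75 per unmatched cell.

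**Between-patient part.** Let matched cells be shifted by d = 0.43. The best additive fit is then d/2 everywhere, leaving residuals of ±d/2. The weighted sum of squares is q = 105 × 0.43²/4 = 4.854.

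**Within-patient part.** Let s be the effect at the three follow-ups, in units of d, with 0 at baseline.
- Planned model (baseline as a level): g = [Σs² − (Σs)²/4]/(1 − ρ).
- Baseline as covariate: g = [Σs² − ρ(Σs)²/(1 + 3ρ)]/(1 − ρ).
- Noncentrality λ = q × g, with 12 numerator df in both. Residual df are 96 × 3 = 288 for the planned test, and 285 after fitting three baseline slopes.
- The difference in g is (Σs)²/[4(1 + 3ρ)]. It is never negative, and it is largest when the effect is sustained.

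**Example at ρ = 0.5, constant effect (1, 1, 1).** Planned: (3 − 9/4)/0.5 = 1.5, so λ = 7.28. Covariate: (3 − 0.5 × 9/2.5)/0.5 = 2.4, so λ = 11.65.

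**Power of the 12-df test from the noncentral F.**

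| Effect at 9 weeks, 6 months, 1 year (SD) | ρ | λ planned | λ covariate | Power planned | Power covariate |
|---|---|---|---|---|---|
| 0.43, 0.43, 0.43 | 0.3 | 5.20 | 10.95 | 25% | 53% |
| 0.43, 0.43, 0.43 | 0.5 | 7.28 | 11.65 | 35% | 57% |
| 0.43, 0.43, 0.43 | 0.7 | 12.13 | 15.66 | 59% | 73% |
| 0.43, 0.43, 0.43 | 0.9 | 36.40 | 39.35 | 99.2% | 99.6% |
| 0.43, 0.215, 0 | 0.5 | 6.67 | 7.77 | 32% | 38% |
| 0.43, 0, 0 | 0.5 | 7.28 | 7.77 | 35% | 38% |

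These are powers for the interaction alone. The rule also requires two non-significant two-way interactions, which is not modelled here.

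**Check by simulation.** At ρ = 0.5, for the matched contrast on the mean of the three follow-ups, theory gives a variance ratio (covariate to change) of (1 + 3ρ)/4 = 0.625. Simulation gave 0.63, and both estimators were unbiased.

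**Averaging over follow-up.** A 4-df treatment-by-classification test on mean follow-up MODI adjusted for baseline has 77% power for the constant effect at ρ = 0.5. It has only 23% for the fading effect and 12% for the effect at nine weeks only. Both are below the planned test.

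**The case against.** The strongest reply is that nothing here is an error. Repeated-measures ANOVA with baseline as a level is valid, and the size of the loss rests on a correlation that the document does not give. That stands: the point is about efficiency only. A reader might infer that the planned analysis is biased or has the wrong false-positive rate, but the documents do not support this. Allocation follows baseline testing, and both estimators target the same matching contrast.

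A second inference to resist is a larger headline gain. At ρ = 0.5, a 4-df test on the mean of the follow-ups rises from 54% (change from baseline) to 77% (baseline as covariate), and a one-sided two-group comparison at one visit from 71% to about 81%. Neither is the test the article specifies, so neither measures its loss. Replacing the planned test by one averaged over follow-up could also lose power. Treatment ends at nine weeks, so a fading effect is plausible.

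Third, it is tempting to say that the pairwise comparisons will be made on raw scores. The article does not say whether they are adjusted, and an analysis plan may settle this, so the silence is not a fault.

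Fourth, the covariate model is not better without conditions. The result above assumes a common baseline slope, and the extra terms use a few degrees of freedom. Removing baseline from the time factor also changes the meaning of the two-way interactions in the decision rule. Classification subgroups are not randomised, so a baseline-adjusted class effect and a class difference in change answer different questions. Those conditions must therefore be rewritten as well.

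The core survives. With the same degrees of freedom for the hypothesis, the covariate version had more power under every effect shape tried at ρ = 0.5.

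**Conclusion.** The concern holds as a loss of precision in a model that the article fixes. Like for like, the 12-df test at ρ = 0.5 gains about 22 points of power for a sustained effect, 6 for a fading one and 3 for an effect at nine weeks only. For a sustained effect the gain is about 28 points at ρ = 0.3 and 14 at ρ = 0.7, and it is negligible near 0.9. All figures assume 105 completers, 0.43 in SDs of the MODI score, equal class sizes for a rule not yet derived, equal correlation between visits and alpha 0.05. The change is worth making because the data will be collected anyway, but it does not correct an invalid analysis.

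**What to change.** In the Validation phase paragraph of Data analysis:
- Take nine weeks, six months and one year as the levels of time.
- Add baseline MODI as a covariate, with a baseline-by-time term.
- Keep treatment group, classification subgroup, their interaction, and the interactions of each with time. Therapies are then compared within class, where they are randomised.
- Test matching jointly through treatment-by-classification and treatment-by-classification-by-time. Make a test averaged over follow-up the principal one only if a sustained effect is the stated hypothesis.
- Restate the two-way conditions of the decision rule as treatment and classification effects on follow-up MODI.
- State that the pairwise comparisons use the same adjusted model.

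The cost is a few residual degrees of freedom and rewording of the hypothesis and decision rule, before validation data exist. No patients, visits or measurements are added.

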### Power analysis

#### Derivation phase

As we cannot predict the therapeutic effect in the derivation phase, we use a two-tailed hypothesis to calculate the power. A pilot study showed that the standard deviation of our primary outcome measure, the MODI, is comparable to the results of Brennan *et al*. [17]. Given these estimates, 120 patients are needed to detect a minimum clinically important difference (effect size 0.43) with 80% power using a two-tailed hypothesis. This means that three groups of 40 patients are needed to complete the whole trial. Since Van der Wouden *et al*. [34] mentioned a dropout rate of 54%, we aim to include 260 patients.

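### The validation success rule has no direction and can cancel a real matching benefit, so it does not test whether matched patients do better than unmatched patients

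*Protocol article*

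**What the plan says.** The protocol article's Data analysis section (Validation phase) plans a repeated-measures analysis of variance of the MODI score. Treatment group (three levels) and classification subgroup (three levels) are between-patient factors; time (baseline, nine weeks, six months, one year) is the within-patient factor. The hypothesis is directional: "such that patients randomized to matched treatment will have better outcomes than patients randomized to unmatched treatment". The criterion for accepting it is: "This hypothesis will be supported if the three-way interaction is significant, but the two-way interactions are not". Pairwise post-hoc comparisons at each follow-up are there only to explore significant interactions further; they are not part of the criterion.

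The Power analysis section (Validation phase) also treats the question as directional, "which means a one-tailed hypothesis is used to calculate the power", and sizes the phase to "detect a minimum clinically important difference (effect size 0.43) with 80% power using a one-tailed hypothesis". It gives 105 evaluable patients. It does not name the test or the alpha, or say whether 0.43 is a standardised difference or Cohen's f.

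**The concern.** The rule and the question do not match, in two ways.

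- **Direction.** An omnibus interaction test asks whether the nine cells change differently over time, not who does better. Matched worse than unmatched satisfies it as readily as matched better.
- **Required non-significance.** Support is withdrawn if time-by-treatment or time-by-classification is significant. Whether matching works does not depend on the therapies being equal overall or on the classes sharing one prognosis. Predictors are selected separately within each arm, so purely prognostic variables can enter a rule, and the resulting classes can then differ in course under any therapy. Nor does a non-significant test show that a difference is absent.

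This rule decides what the validation phase concludes. Read literally, it can endorse matching that harms and reject matching that helps. For a given overall difference, a larger sample makes the second failure more likely.

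**Working it through.** **Inputs from the protocol.** 3 treatments × 3 classes × 4 time points; 105 evaluable patients; effect size 0.43; 80% power, one-tailed; matched to unmatched 50:50 within each arm (Randomization and blinding); treatment success defined as a 6-point fall in MODI (Data analysis, Derivation phase).

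**Assumptions.** Alpha 0.05 (stated only for the derivation regression); SD 14, inferred from 6/0.43 = 13.95; compound symmetry with correlation ρ of 0.3, 0.5 or 0.7; effect constant over the three follow-ups.

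**1. Degrees of freedom.** Three-way: (3−1)(3−1)(4−1) = 12. Each two-way interaction with time: (3−1)(4−1) = 6.

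**2. Reproducing the stated 105.**
- Two-group comparison at d = 0.43, one-sided: 2(1.645 + 0.842)²/0.43² = 66.9, so 67 per group and 134 in total. Two-sided: 85 per group, 170 in total. Neither gives 105.
- 12-df F-test over nine cells with 0.43 as Cohen's f: λ = f²N = 0.1849 × 105 = 19.41, error df 105 − 9 = 96, power 80.4%. This reproduces 105. At alpha 0.025 it needs 121, against the 120 stated for the derivation phase.
- Dropout: 105/0.46 = 228.3, so 229, as stated.

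**3. Direction.** Suppose matching shifts MODI by d SDs at every follow-up and not at baseline. The pattern (0, d, d, d) has sum of squares 0.75d² about its mean, and the error variance of the time contrasts is 1 − ρ in SD² units. With a 50:50 split balanced over arms and classes,

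λ = [0.75d²/(1 − ρ)] × N/4.

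Only d² enters, so the sign of the effect drops out. Simulation with 108 completers (three matched cells of 18, six unmatched cells of 9) agrees:

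| True effect of matching | Rule met, ρ = 0.5 | Rule met, ρ = 0.7 |
|---|---|---|
| 6 points better | 32% | 52% |
| 6 points worse | 33% | 53% |

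**4. Power if 0.43 is a standardised difference, N = 105.** Error df 3(105 − 9) = 288.

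| ρ | λ | Three-way test, from λ | Full rule (simulated) | N for 80% on three-way test |
|---|---|---|---|---|
| 0.3 | 5.20 | 25% | 22% | 354 |
| 0.5 | 7.28 | 35% | 30% | 254 |
| 0.7 | 12.13 | 59% | 53% | 154 |

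If 0.43 is Cohen's f, the three-way test has 80%. Requiring two further true-null tests to be non-significant leaves about 0.80 × 0.95² = 0.72.

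**5. Cost of the two-way condition.** Percentage of trials meeting the rule with 108 completers, ρ = 0.5, and class prognosis of −s, 0, +s points:

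| Benefit of matching | s = 0 | s = 3 | s = 5 |
|---|---|---|---|
| 6 points | 32% | 25% | 8% |
| 12 points | 88% | 66% | 25% |

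In the last cell the three-way test itself is significant in 97% of trials. At ρ = 0.7 it is significant in 100% and the rule is met in 6%.

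Unequal benefit across the three rules does the same. If only one rule works (1.29 SD; N = 105, ρ = 0.5), the three-way test is significant in 63% of trials but the full rule is met in 22%, because the inequality itself creates two-way interactions.

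**6. One directional contrast instead.** Matched minus unmatched on mean follow-up minus baseline, adjusted for treatment and class, one-sided 0.05, N = 105, d = 0.43: power 74%, 85% and 97% at ρ of 0.3, 0.5 and 0.7. At ρ = 0.5 it stays near 85% when a therapy or class differs overall, and it is 0% when matching harms.

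**The case against.** **The trial may have been sized for exactly this test.** A reader might infer that the analysis is simply underpowered. The protocol does not support that flatly: with 0.43 as Cohen's f, the stated 105 is what the 12-df test needs. The wording about a minimum clinically important difference points towards a standardised difference, but does not settle it. The power statement must stay conditional on the reading.

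**The rule does not fail every time a therapy or class differs overall.** A reader might infer that it does. It fails only when such a difference reaches significance. A ±3-point class spread costs a modest amount; near-total loss needs a large spread, and no figure in the protocol supports one particular spread. This stands.

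**Harm would be noticed.** The criterion refers back to a hypothesis that says matched patients do better, and the post-hoc comparisons would show a reversal. It is fair not to infer that the investigators would in fact announce support for harmful matching. But those comparisons lie outside the rule, so the gap in the criterion remains.

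**The two-way conditions belong to the stated hypothesis.** The protocol does predict no overall difference by treatment or class, so the rule is not self-contradictory. But the aim in the Abstract, Study design and Power analysis is matched better than unmatched, without those conditions, and failing to reject does not establish them.

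**The advantage of a contrast is a favourable case.** This is partly right. If the effect fades over the visits (full, half, quarter; ρ = 0.5), its power is 47%, against 23% for the current rule.

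**Conclusion.** The concern holds for the structure of the rule. Its lack of direction and its dependence on two non-significant tests follow from the stated criterion and need no simulation. The sizes are conditional. With SD 14, ρ = 0.5, a constant effect, compound symmetry and alpha 0.05, harm and benefit of 6 points meet the rule about equally often. A 6-point benefit loses a quarter of its chance of support at ±3 points of class spread (32% to 25%) and three quarters at ±5 (32% to 8%). Power for the full rule is about 72% on one reading of 0.43 and 22% to 53% on the other; the protocol does not say which applies. This should be settled before validation data exist, because it determines what that phase can conclude.

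**What to change.** **Data analysis, Validation phase**
- Make the primary test one pre-specified matched-minus-unmatched contrast in MODI over the follow-up visits, adjusted for baseline MODI, treatment group and classification subgroup. Report the estimate and confidence interval, and require the contrast to favour matched.
- Delete the condition that the two-way interactions be non-significant and report those interactions descriptively.
- Show the matched-unmatched estimate for each therapy's rule beside the pooled one, because the Abstract aims to validate a rule for each therapy.

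**Power analysis, Validation phase**
- State the effect-size type, test and alpha, and restate the power of 105 patients for the new contrast.

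**Cost.** No new data are needed, but this is more than a wording change: the stated 105 reproduces for the 12-df F-test and not for a two-group comparison at d = 0.43, so the sample-size basis must be recalculated. The pooled contrast also assumes a broadly similar benefit across rules and visits. It loses power if the effect fades, and it can be positive because one rule works: 83% of simulated trials in the one-rule scenario (1.29 SD, ρ = 0.5). The per-rule estimates therefore have to be reported with it.
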